### Primary efficacy outcomes

*Hypothesis 1 (acute outcomes): Adolescents receiving pre-operative CBT will have a faster rate of recovery of pain severity and interference during the 14 days following hospital discharge, compared to adolescents who receive pre-operative education.* The acute outcomes will be assessed before any post-operative intervention has taken place. Therefore, arms 1 and 3 will be combined into the control group (pre-operative education); arms 2 and 4 will be combined into the intervention group (receiving pre-operative CBT intervention) for this analysis (see Table 4). We will apply nonlinear mixed effects models with an exponential decay functional form, to evaluate individual rate of recovery in daily pain severity and interference, or how quickly the process decays/improves from the initial value to the asymptote. Rate parameters will be estimated using restricted maximum likelihood (REML) approach and compared using multivariate Wald test. As a further primary analysis, we will treat daily pain severity and interference as repeated measures using generalized estimating equations (GEE) to account for clustering within participants.

**Table 4 Tab4:** Treatment arms

Group	Pre-operative phase	Post-operative phase
1	ED	ED
2	CBT	ED
3	ED	CBT
4	CBT	CBT

*ED* online education, *CBT* Cognitive Behavioral Therapy Intervention

*Hypothesis 2 (chronic outcomes): Adolescents receiving post-operative CBT alone will have lower pain severity and interference, compared to adolescents receiving education control at 3 months.* We will consider the education control arm (arm 1) as the control group and post-operative CBT alone arm (arm 3) as the intervention group. Covariates adjusted linear regression models will examine group differences in average pain severity and interference, as continuous outcomes, at 3 month follow-up.

*Hypothesis 3 (chronic outcomes): Adolescents receiving both phases of peri-operative CBT will have lower pain severity and interference compared to adolescents receiving single phase (pre- or post-surgery) intervention or education control alone at 3 months.* We will apply linear regression models to examine differences in average pain severity and interference between individual study arms, treated as a 4-level categorical predictor variable.

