### Assessment plan

All assessments will be completed online through the REDCap database [29] via email/text survey links. Youth and parents will complete a baseline assessment prior to randomization (T1, baseline). Following hospital discharge from surgery, adolescents will complete daily assessments for 14 days (T2, acute outcomes). Adolescents will report on daily pain outcomes for 7 days and adolescents and parents will complete additional outcome measures at 3 months (T3, chronic outcomes) and 6 months (T4, final follow-up) post-surgery. Participants will receive email or phone reminders by study staff to complete survey measures. Automated REDCap alerts will also be used to inform study coordinators about missing data so they can follow-up with participants to obtain responses. Additionally, participants are provided with an Amazon gift card for completing each assessment.

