### Data analysis

The primary analyses will be intent-to-treat analyses which will include all participants randomized, with adolescent as the unit of analysis. All regression analyses will adjust for a priori identified demographic variables (age, sex, race/ethnicity), prognostic covariates (pre-surgery pain intensity), and study site. Separate models will be conducted to analyze pain severity and pain interference (primary outcomes), as assessed by the BPI. For multi-item instruments, published rules on treatment of missing data will be followed where available; otherwise, hot deck imputation will be used for individual items for less than 20% missing data. There are no interim analyses planned.

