### Sample size and power calculations

Power calculations on primary pain outcomes are based on data available from our preliminary peri-operative studies [4, 7, 31] and from prior peri-operative intervention studies [16–18]. Power analyses for primary acute outcomes were based on rate of recovery using an exponential decay model. Based on pilot data, we assume log(rate) = − 1.21 (SE = 0.38) in the intervention arm, which translates into a half-life (days taken to achieve 50% reduction in BPI outcome from time 0) of 4.13 days. Using a conservative estimate of 35% increased half-life of recovery in the control arm, 31 subjects per arm would provide 90% power; N = 24/arm for 80% power.

For the second acute parameter of interest, power calculations were performed using GEE model on time-averaged difference (TAD) using individual daily repeated measures of BPI scores. In order to detect a group difference of 1.2 with standard deviation 2.0, we need to enroll 199 participants into each of the two comparison groups (total sample of 398; assuming 1:1 allocation of subjects into pre-operative education vs. intervention, within-subject observations follow AR(1) correlation pattern with a correlation coefficient of 0.7, and a missing completely at random rate of 5% each day).

For the primary chronic pain outcomes, to detect a group difference of 1.0 with standard deviation 1.8, 35 subjects are needed per arm for 80% power based on two-sample t test.

The target complete sample is 400 adolescent/parent dyads. Conservatively accounting for 20% attrition, we plan to enroll 500 adolescents but will adjust this if completion rates are > 80%.

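### If missed diary days follow earlier pain differently by arm, the GEE estimate of the 14-day pain difference depends on its working correlation; a likelihood model or weights would be a cheap safeguard

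*Protocol article*

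**What the plan says.** Under Assessment plan, after discharge "adolescents will complete daily assessments for 14 days (T2, acute outcomes"). Primary efficacy outcomes, Hypothesis 1, compares pre-operative CBT (arms 2 and 4) with pre-operative education (arms 1 and 3) in two ways:

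- A recovery-rate model: "We will apply nonlinear mixed effects models with an exponential decay functional form", with "Rate parameters will be estimated using restricted maximum likelihood (REML) approach and compared using multivariate Wald test".
- "As a further primary analysis", a GEE on the daily scores: "we will treat daily pain severity and interference as repeated measures using generalized estimating equations (GEE) to account for clustering within participants".

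Sample size and power calculations treats the GEE target as a time-averaged difference. It assumes that "within-subject observations follow AR(1) correlation pattern with a correlation coefficient of 0.7" and "a missing completely at random rate of 5% each day". This is the only missingness assumption stated for whole diary days. The missing-data rule under Data analysis concerns items within an instrument. The same section promises "intent-to-treat analyses which will include all participants randomized". No working correlation or weighting is named for the analysis itself.

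**The concern.** The diary starts the day after discharge from spinal fusion, so a lapse on one day may well be related to pain on the days before. The groups also arrive with different experience. CBT participants have used an app with daily symptom ratings and push notifications, while controls have used an education website. If the link between pain and lapsing differs between the groups, the participants still reporting are selected differently by arm.

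An unweighted GEE then keeps its usual robustness to a wrong working correlation only for the standard error, and loses it for the point estimate. At stake is the size of the estimated pre-operative CBT effect, for both severity and interference, in an analysis labelled primary. The recovery-rate model is likelihood-based but does not fill the gap, because it estimates a rate and not the 14-day difference.

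**Working it through.** **1. The plan's own figure.** For a time-averaged difference, n per group = 2 × SD² × (z_α + z_power)² × v / Δ². From the article, SD = 2.0 and Δ = 1.2. The factor v is the variance of the 14-day mean relative to SD². It equals 0.330 under AR(1) 0.7 with 5% of days missing. Alpha and power are not stated for this calculation, so two-sided 0.05 is assumed.

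- 80% power: 8 × 7.849 × 0.330 / 1.44 = 14.4, so 15 per group.
- 90% power: 8 × 10.507 × 0.330 / 1.44 = 19.3, so 20 per group.

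The stated 199 per group does not reproduce. That is a separate matter and plays no part in the bias argument. It gives a yardstick: at 199 per group the standard error is √(8 × 0.330 / 199) = 0.115.

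**2. Why the working correlation matters.** With an identity link, GEE solves Σ Xᵢ′Vᵢ⁻¹(Yᵢ − Xᵢβ) = 0 over observed days. With V taken as independence, each day's contrast compares whoever reported that day, and earlier scores carry no information about the missing ones. With V equal to the true covariance, the equation is the one that Gaussian likelihood solves for β, and earlier scores do inform the missing days.

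**3. Simulations.** All use 14 days and SD 2.0. Every dropout mechanism is assumed.

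*(a)* 200 per group, true difference −0.60, dropout dependent on pain in control only, 71–87% of control days and 83–93% of CBT days observed:

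- Independence GEE: −0.32 to −0.53, a loss of 0.28 to 0.07 (47% to 12% of 0.60).
- AR(1) GEE with a participant intercept in the truth: −0.49 to −0.53, a loss of 0.11 to 0.07 (18% to 12%).
- Exchangeable GEE with correlation fixed at 0.6, pure AR(1) truth: −0.67 to −0.75.
- Likelihood model with estimated unstructured covariance: −0.59 to −0.62 throughout, with almost no loss of precision.

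*(b)* A milder contrast: 1,000 participants, true difference −0.60, intercept plus AR(1). The log-odds of dropout per point of the previous day's pain are 0.5 in control and 0.25 in CBT, with 78% and 84% of days observed. Independence gave −0.42, AR(1) −0.49 and the correct-covariance fit −0.58 (Monte Carlo SE 0.01–0.02).

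*(c)* Bias under no treatment effect: 199 per group, 400 runs, log-odds 1 per SD of the previous day's pain (Monte Carlo SE 0.006–0.008):

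| Missingness | True correlation | Independence | AR(1) | Exchangeable |
|---|---|---|---|---|
| 5% per day, completely at random | AR(1) 0.7 | 0.00 | 0.00 | 0.00 |
| Opposite dependence by arm, about 5% baseline loss | AR(1) 0.7 | +0.05 | 0.00 | −0.01 |
| Control only, about 20% baseline loss | AR(1) 0.7 | +0.08 | 0.00 | −0.01 |
| Opposite by arm, about 20% (extreme) | AR(1) 0.7 | +0.17 | +0.01 | −0.02 |
| Opposite by arm, about 20% (extreme) | intercept plus AR | +0.30 | +0.16 | 0.00 |

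In the last two rows a Gaussian likelihood fit had bias −0.03 and 0.00 (60 runs, Monte Carlo SE 0.016 and 0.02).

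**4. Effect on the test.** The empirical standard error in (c) is 0.006 × √400 = 0.12. A bias of 0.08 is 0.08 / 0.12 = 0.67 standard errors, which takes a nominal 5% two-sided test to about 10%. A bias of 0.166 (the +0.17 above) is 1.38 standard errors, or about 28%.

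**5. Where it is small.** When dropout depends on pain alike in both arms, estimates for a truth of −0.60 ran from −0.53 to −0.62. The planned loss is 14 × 0.05 = 0.7 days per participant, well below the losses in (a).

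**The case against.** A reader might infer that GEE is valid only if diary days are missing completely at random, and hence that the planned analysis is invalid. The documents do not support this. GEE also tolerates missingness explained by modelled covariates, and Data analysis lists age, sex, race/ethnicity, pre-surgery pain and site. With a good working correlation it behaves almost like a likelihood fit. Under AR(1) 0.7, the only correlation the article states, AR(1) GEE was nearly unbiased. Exchangeable GEE was nearly unbiased under intercept plus AR(1). The article names no working correlation, so the most biased version is not one it prescribes.

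The design also argues against a large arm difference. No programme runs during the diary window, since the post-operative phase starts 3 weeks after surgery. Reminders, missing-data alerts and gift cards apply to everyone, and the control condition is built to match time, attention and online usage. Working correlation and missing-day handling may properly sit in a SAP that is not shown, and complete randomness is a routine simplification in a power calculation.

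All of this stands, and it limits the point. One counter-argument does not stand: that a likelihood fit looks better only because it was given the true covariance. In (a) the covariance was unstructured and estimated, and the result stayed at −0.59 to −0.62. No single simple working correlation did well in every setting. Exchangeable, the best under intercept plus AR(1), overshot in (a) under pure AR(1) with its correlation fixed at 0.6, although other runs under pure AR(1) put it at −0.61 to −0.63.

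**Conclusion.** The point holds as a cheap robustness improvement to a stated primary method. If lapses follow earlier pain differently by arm, and losses are well above the planned 5%, a poorly matched working correlation moves a true difference of −0.60 by roughly 0.07 to 0.28 points. The bias is towards no effect when the dependence is in control, and by symmetry away from it when the dependence is in the CBT group. The bias is near zero under the planned missingness. It is close to zero when the working correlation suits the data, and small when dropout acts alike in both arms or losses are near 5%.

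The result rests on assumed dropout mechanisms and on a participant-level intercept being plausible in daily pain scores. The article gives data on neither. It would also be too strong to say that the two Hypothesis 1 analyses could disagree only because of missing days. They target different quantities, a recovery rate and a time-averaged difference, and can differ with complete data.

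**What to change.** Estimate the same 14-day average treatment contrast with a likelihood-based repeated-measures mixed model: categorical day, treatment, the covariates already listed, and an unstructured or random-intercept-plus-AR(1) covariance. Alternatively, keep the GEE and weight each observed day by the inverse probability of completion given earlier pain and arm. If the SAP already does either, nothing further is needed.

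The cost is a few lines of SAP text and standard software, with no change to data collection or sample size. The small downside is that the mixed model relies on an adequate mean and covariance model; robust standard errors can be kept. Neither option protects against missingness that depends on the unobserved pain itself.

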### Trial design and randomization

This study will utilize a single-blinded, randomized 2 × 2 factorial design (see Fig. 1). Block randomization will be used to allocate participants to one of four arms with random block sizes, stratified by participant sex. The randomization allocation table will be implemented using the REDCap randomization framework using an allocation ratio of 1:1:1:1 and will occur directly before treatment assignment. The randomization process will be overseen by an independent statistician, who is not involved with study procedures, including participant recruitment, intervention assignment, or any other forms of participant contact. Randomization results will only be directed to the study coordinator, who will assign participants to the intervention groups. All other study staff including the trial investigators, and data analyst will be blinded to treatment assignment. Care providers will not be informed of treatment assignment, and participation in the study will not affect clinical care. Participants may therefore engage in any other intervention or treatment (e.g., counseling, physical therapy). In the unlikely event of an adverse event, unmasking would be permissible.

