## Discussion

This study will address a critical gap in knowledge of perioperative interventions targeting psychosocial risk factors to prevent transition from acute to CPSP in adolescents undergoing spinal fusion surgery. Our trial will use an innovative factorial design to test two intervention phases, pre-operative and post-operative, in order to determine the optimal timing of intervention delivery. This study will build on prior research examining short-term efficacy of peri-operative psychosocial interventions to reduce acute pain intensity by testing improvement on clinically meaningful and longer-term post-surgical outcomes such as chronic pain interference and quality of life. In addition, our recruitment design across multiple pediatric spine centers allows for broad inclusion of youth undergoing spinal surgery at community and academic hospital sites in many different regions of the USA.

To engage wide participation in a peri-operative program, interventions must use flexible, accessible, low-cost delivery models. Research with family stakeholders indicates that teens and parents prefer technology-based delivery within the current system of peri-operative care [45]. To address these needs, we developed the CBT and education interventions to be flexibly delivered via a mobile application and website for deployment in the trial. If successful, following the trial, we will have the unique opportunity for widespread dissemination of the SurgeryPal^TM^ interventions to adolescents receiving care in pediatric spine centers across the country.

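### Take the Hypothesis 2 contrast from the four-arm model that Hypothesis 3 already fits, and state the phase effects and arm 4 contrasts that address timing at 3 months

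*Protocol article*

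**What the plan says.** The trial is a 2 × 2 factorial with "an allocation ratio of 1:1:1:1" (Protocol article, Trial design and randomization). Arm 1 is education in both phases, arm 2 pre-operative CBT only, arm 3 post-operative CBT only, and arm 4 CBT in both phases.

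Under Primary efficacy outcomes:
- Hypothesis 1 (acute pain) pools across the post-operative factor, arms 2 and 4 against arms 1 and 3.
- Hypothesis 2 (3-month pain) concerns post-operative CBT alone: "We will consider the education control arm (arm 1) as the control group and post-operative CBT alone arm (arm 3) as the intervention group". The analysis is a covariate-adjusted linear regression. Nothing says that arms 2 and 4 stay in the model.
- Hypothesis 3 (3-month pain) is that both phases give lower pain than either single phase or education. It is analysed by "linear regression models to examine differences in average pain severity and interference between individual study arms, treated as a 4-level categorical predictor variable".

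The Data analysis section adjusts all regressions for age, sex, race/ethnicity, pre-surgery pain and study site. The only interactions mentioned, under Secondary analyses, are with sex, race and ethnicity. The Discussion says that the factorial design was chosen "in order to determine the optimal timing of intervention delivery".

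**The concern.** Two things stand out.

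First, Hypotheses 2 and 3 use the same outcome at the same time, yet Hypothesis 2 appears to be fitted on half the data. With some 19 to 25 sites in the model, a 200-person fit spends a noticeable share of its information on site and covariate coefficients that the other 200 participants could help to estimate.

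Second, the 3-month hypotheses do not name the comparisons that bear on timing: the pre-operative effect (arm 2 against arm 1), pre against post (arm 2 against arm 3), the phase main effects and their interaction. Hypothesis 3 makes a directional claim about arm 4 but does not say which contrasts must succeed. A reader of the results could then take evidence that some arm differs from education as evidence that a second phase is worth adding.

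**Working it through.** **Inputs.** From Sample size and power calculations: "to detect a group difference of 1.0 with standard deviation 1.8", and "The target complete sample is 400 adolescent/parent dyads", which at equal allocation is about 100 per arm. From Participants and setting: 19 active sites, about 25 expected. Assumed, because the article gives no alpha: 0.05 two-sided. Also assumed: site as fixed effects and about 4 further covariate columns.

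**1. The plan's own figure.** The article says "35 subjects are needed per arm for 80% power based on two-sample t test". Normal approximation: n = 2 × (1.96 + 0.84)² × (1.8/1.0)² ≈ 51 per arm; the exact t test gives 52. At 35 per arm, power is 0.63. The stated figure does not reproduce at this alpha (one-sided 0.05 gives 41). That is a separate matter and does no harm here, since 100 per arm exceeds 52.

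**2. Hypothesis 2 as written, unadjusted.** SE = 1.8 × √(2/100) = 0.255. Power at a difference of 1.0 is 0.974, and the difference detectable with 80% power is 0.72.

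**3. Same contrast, two-arm against four-arm fit.** With p nuisance columns in N participants, the variance of the contrast is inflated by roughly 1/(1 − p/N). Using about 198 and 396 for N after the arm terms:
- 25 sites, p = 24 + 4 = 28: variance ratio, four-arm to two-arm, = (1 − 28/198)/(1 − 28/396) = 0.859/0.929 = 0.92.
- 19 sites, p = 18 + 4 = 22: (1 − 22/198)/(1 − 22/396) = 0.889/0.944 = 0.94.

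The reduction is therefore about 6–8%. Design simulation with 25 sites agrees: the SE falls from 0.276 to 0.265, and (0.265/0.276)² = 0.92. Multiplying by 2.8, the detectable difference moves from about 0.77 to 0.74.

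**4. The pooled post-operative effect (arms 3 + 4 against 1 + 2).** Unadjusted SE = 1.8 × √(2/200) = 0.18, detectable difference 0.51. This is a different estimand. If the second phase adds nothing, the effect is −1.0 without pre-operative CBT and 0 with it, so the pooled effect is −0.5. Power is then about 0.79, against 0.974 for arm 3 against arm 1.

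**5. Hypothesis 3: what each test would show.** Let arms 2, 3 and 4 all lie d below arm 1, so that the second phase adds nothing. At d = 1.0 the noncentrality is 100 × (0.75² + 3 × 0.25²)/1.8² = 23.1, and the F test on 3 and 396 degrees of freedom has power 0.988. At d = 0.75 it is 0.87, and at d = 0.5 it is 0.50.

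Simulation at 100 per arm (200,000 runs), with means listed for arms 1 to 4:

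| True means | Overall test | Arm 4 below arm 1 | Arm 4 below both arms 2 and 3 |
|---|---|---|---|
| 0, −1, −1, −1 | 0.99 | 0.975 | 0.005 |
| 0, −1, 0, −1 | 0.998 | 0.974 | 0.025 |
| 0, −1, −1, −2 | 1.00 | 1.00 | 0.955 |
| 0, −0.5, −0.5, −1 | 0.92 | 0.975 | 0.33 |

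The entries for arm 4 require two-sided significance in its favour. A rule that asks only for the point estimates to favour arm 4 would not do: in the first row, arms 2, 3 and 4 are exchangeable, so arm 4 comes out lowest about one time in three.

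**The case against.** A reader might infer that Hypothesis 3 will be declared on an overall F test. The article does not say so. It speaks of differences between individual arms, and the hypothesis itself names the comparators. Coding arm as a four-level factor describes the predictor, not the decision rule, and pairwise contrasts from that model each have the correct 2.5% error in one direction against a single-phase arm. The exploratory analysis of chronic postsurgical pain likewise compares arm 4 with arms 1, 2 and 3. Exact contrasts may also stand in the unseen analysis plan. All of this stands, so the 99% shows what an overall test could not support; it is not a prediction of what the trial will do.

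A reader might also infer that Hypothesis 2 is underpowered or should be replaced by the pooled post-operative effect. Neither follows. Arm 3 against arm 1 is the correct estimand for post-operative CBT alone, its power is ample at the design difference, and pooling loses power when the second phase adds little.

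Finally, the four-level model is saturated: it has the same fit as two phases plus their interaction, and every timing contrast can be drawn from it. So the long-term pre-operative effect is not beyond the trial's reach. What remains is that the article does not name these comparisons and does not use that model for Hypothesis 2.

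**Conclusion.** The point holds as an improvement at little cost. Hypothesis 2 keeps its estimand and gains about 6–8% in variance if it is taken from the four-arm fit. The gain depends on site entering as fixed effects and on the number of covariate columns, and it is modest. The 3-month hypotheses should name the phase effects, the interaction and the single-phase contrasts, because the article gives timing as the reason for the factorial design.

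A claim that two phases beat one needs arm 4 to be significantly lower than both arm 2 and arm 3. Neither an overall test nor the arm 4 against arm 1 contrast alone can carry it. The figures rest on SD 1.8, 100 completers per arm, an assumed two-sided alpha of 0.05 and, for the Hypothesis 3 simulation, no covariate adjustment.

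**What to change.** For each 3-month primary outcome, fit one model on all four arms, adjusted for the stated covariates and site. From it:
- **Hypothesis 2:** keep arm 3 minus arm 1, estimated within this model.
- **Hypothesis 3:** report arm 4 against arms 1, 2 and 3. Claim that two phases beat one only if arm 4 is significantly lower than both arm 2 and arm 3.
- **Timing, labelled supportive:** report the pre- and post-operative main effects together with their interaction, and the arm 2 against arm 1 and arm 2 against arm 3 contrasts.

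This changes analysis wording only; no data or participants are added. There are three costs. The Hypothesis 3 claim becomes stricter: power is 0.955 if each phase adds 1.0 but only 0.33 if each adds 0.5. The main effects must be read with the interaction, which is itself imprecise: its SE is 1.8 × √(4/100) = 0.36, so about 2.8 × 0.36 = 1.0 is detectable with 80% power. And the four-arm fit assumes common covariate effects and residual variance across arms, as Hypothesis 3 already does.
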